### Research ethic approval

The study adheres to the Declaration of Helsinki on medical research protocols and ethics. The protocol was reviewed and approved by the Human Medical Ethics Committee of the Sixth Affiliated Hospital of Sun Yat-sen University (number 2022ZSLYEC-614).

### Confidentiality

Patient confidentiality will be strictly maintained.

### Dissemination policy

The final study results will be published in peer-reviewed scientific journals. Furthermore, results will be communicated through professional meetings and the media.

## Discussion

This paper presents a protocol for a prospective, observational, controlled, multicentre study to dynamically evaluate the different roles of NCRT with surgery, NCT with surgery and surgery only on the anorectal function of LARC patients. There are similar studies published, but their main objective was to clarify the short-term or long-term contribution of neoadjuvant chemoradiotherapy and/or surgery on the impairment of anorectal function in patients with rectal cancer [12, 25, 26]. The most recent study has reported that the rectal adenocarcinoma patients undergoing neoadjuvant therapy were submitted to functional evaluation by anorectal manometry and the degree of FI using the Wexner continence score, before and eight weeks after NCRT [27]. Besides that, a prospective study has performed anorectal manometry preoperatively and a median of 384 days postoperatively to evaluate the impact of NCRT on anal sphincter function [28].

Major anorectal dysfunction is common in patients with rectal cancer undergoing sphincter-saving treatment. Long-term follow-up of patients and continued symptom assessment is necessary to improve the treatment of major anorectal dysfunction. Unlike most previous studies, our study will dynamically assess the changes of anorectal function in patients with rectal cancer before and after sphincter-saving treatment and at follow-up visits and further evaluate the different roles of NCRT, NCT and surgery in determining anorectal dysfunctions. Focusing on the dynamic effects of different treatments for anorectal function will provide more information on therapeutical options and strategies to reduce anorectal dysfunction.

Our study will use high-resolution anorectal manometry to evaluate anorectal function, which is widely used in clinical studies. Although Dulskas A et al. found that anorectal manometry might be insufficient to properly capture LARS [29]. Kitaguchi D and colleagues reported that high-resolution anorectal manometry was reliable for the evaluation of anorectal function after intersphincteric resection [13]. Hence, anorectal manometry can be used as an appropriate tool for evaluating anorectal dysfunctions in patients with rectal cancer.

There are some limitations in this study. The study design is observational but not randomized and blinded. At the end of the study, we will stratify the patients according to age, sex, and cancer stage. After completing the recruitment and preliminary evaluation, we will further determine whether to enlarge the sample size or not.

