#### Participants

Patients diagnosed with LARC at The Sixth Affiliated Hospital, Sun Yat-sen University and Nanfang Hospital, Southern Medical University will be assessed for suitability for inclusion.

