#### Outcomes

Evaluations will take place at baseline (T1), after radiotherapy or chemotherapy (before surgery, T2), after surgery (before closing the temporary stoma, T3), and at follow-up visits (every 3 to 6 months, T4, T5……). Follow-up for each patient will be at least 2 years.

The primary outcome is the average resting pressure (ARP) of anal sphincter. The secondary outcomes are maximum anal sphincter contraction pressure, Wexner continence score and LARS score. We will use high-resolution anorectal manometry (Solar GI HRM; MMS, Enschede, the Netherlands) to assess the average resting pressure and maximal contraction pressure, which has proven to be adequate for clinical use [23, 24]. This test will be performed by the trained physicians. In addition, we will use Wexner continence score and LARS score to assess fecal incontinence symptoms of patients following sphincter-preserving rectal cancer surgery.

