### Allocation

The study is a prospective, observational, controlled study without randomization. Treatment decisions will be made by multidisciplinary team for eligible patients who voluntarily sign the consent form. All patients will receive evaluation of the anorectal function through anorectal manometry, Wexner continence score and LARS score before and after therapies and at follow-up visits.

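### The stratification factors named for this non-randomised two-hospital study leave out centre, so a hospital difference in resting pressure could be counted as a treatment effect

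*Protocol article*

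**What the plan says.** - **Sites.** The Participants section draws on two hospitals: "Patients diagnosed with LARC at The Sixth Affiliated Hospital, Sun Yat-sen University and Nanfang Hospital, Southern Medical University".
- **Allocation.** There is no randomisation. "Treatment decisions will be made by multidisciplinary team for eligible patients who voluntarily sign the consent form". The Interventions section adds that treatment follows guidelines.
- **Primary outcome and measurement.** "The primary outcome is the average resting pressure (ARP) of anal sphincter". One system is named for the study, "high-resolution anorectal manometry (Solar GI HRM; MMS, Enschede, the Netherlands", and one examination procedure is described. On who does it, the Outcomes section says only: "This test will be performed by the trained physicians".
- **Analysis.** The Statistical methods section gives t or Mann-Whitney tests between groups and paired t or Wilcoxon tests within patients. No covariate or stratum is mentioned there.
- **Confounder control.** The limitations paragraph of the Discussion notes that the study is neither randomised nor blinded and continues: "At the end of the study, we will stratify the patients according to age, sex, and cancer stage".

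Centre appears neither in the Statistical methods section nor in that list.

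**The concern.** The study aims to separate the roles of chemoradiotherapy, chemotherapy and surgery, which requires comparisons between groups. Nothing in the design balances the three strategies within each hospital. Suppose one hospital has lower resting pressures, for whatever reason, and also contributes a larger share of the chemoradiotherapy group. The unadjusted comparison then attributes part of the hospital difference to radiotherapy. The opposite mix would mask real damage. Stratifying by age, sex and stage does not remove a difference between hospitals among patients alike on those three factors. Centre is known for every patient, so leaving it off the list gains nothing.

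**Working it through.** **The plan's own figure.** The Sample size section takes 32.7 (SD 17) against 45.3 (SD 18) mmHg, 80% power and alpha 0.05, and states 122 per group.
- Difference = 45.3 − 32.7 = 12.6 mmHg.
- Pooled SD = √((17² + 18²)/2) = 17.51 mmHg.
- The normal two-sample formula gives 31 per group (two-sided) and the exact t test 32, so 122 does not reproduce. That is a separate matter. Here 122 is used only as the planned analysable number per group.

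**Assumed inputs.** The documents give neither the hospital offset in resting pressure nor the treatment mix by hospital. Offsets of 2 and 5 mmHg are assumed. A share of 60/40 means that 60% of one treatment group and 40% of the other come from the same hospital. The calculation covers one pair of groups with no true treatment effect.

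**Bias and false-positive rate, unadjusted comparison.**
- Bias = offset × (p₁ − p₂), where p₁ and p₂ are that hospital's shares in the two groups.
- SE = √[(2 × 17.51² + offset² × (p₁(1 − p₁) + p₂(1 − p₂)))/122].
- False-positive rate = P(|Z + bias/SE| > 1.96).

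| Offset (mmHg) | Shares | Bias (mmHg) | SE (mmHg) | Bias as % of 12.6 | False-positive rate |
|---|---|---|---|---|---|
| 2 or 5 | 50/50 | 0 | 2.25 to 2.26 | 0% | 5.0% |
| 2 | 60/40 | 2 × 0.20 = 0.4 | 2.25 | 3% | 5.4% |
| 2 | 80/20 | 2 × 0.60 = 1.2 | 2.24 | 10% | 8.3% |
| 5 | 60/40 | 5 × 0.20 = 1.0 | 2.26 | 8% | 7.3% |
| 5 | 80/20 | 5 × 0.60 = 3.0 | 2.26 | 24% | 26.5% |

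**Precision with centre in the model.** A constant hospital offset then drops out. The standard error is 17.51/√(Σ n₁n₂/(n₁ + n₂)), summed over the two hospitals, where n₁ and n₂ are the two groups' numbers in each hospital.
- 50/50: 2 × (61 × 61/122) = 61.0, SE 2.24 mmHg.
- 60/40: 2 × (73.2 × 48.8/122) = 58.56, SE 2.29 mmHg.
- 80/20: 2 × (97.6 × 24.4/122) = 39.04, SE 2.80 mmHg.
- 90/10: 2 × (109.8 × 12.2/122) = 21.96, SE 3.74 mmHg.

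Even at 90/10, power for 12.6 mmHg is Φ(12.6/3.74 − 1.96), about 92%.

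**The case against.** **An analysis plan may cover this.** Centre as a covariate is typical content for a statistical analysis plan, which is not shown. The quoted sentence sits among the limitations and does not claim to be exhaustive. If the article were simply silent on adjustment, that would settle it. It is not silent: it names its factors, directly after conceding the lack of randomisation, and a named list can be reviewed. An unseen plan may nevertheless already include centre.

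**The protocol has mitigations.** A single device and a single procedure may shrink any reading offset, and a constant offset cancels in the paired tests. A between-group comparison of change from T1 would cancel it too. This stands for the measurement part. However, the plan does not commit the group comparisons to change scores, and the sample size rests on absolute resting pressure at ileostomy closure. Neither pairing nor change scores remove a hospital difference that arises after baseline, for example from surgery.

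**Both inputs are assumed.** This stands. The figures show what could happen, not what will.

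**Selection by patient and tumour may be the larger threat.** Adjusting for centre does not deal with that. This also stands, but it is no reason to leave centre out.

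**Stronger readings.** A reader might infer that different operators perform manometry at each hospital, or that each hospital chooses treatment separately. The documents say neither. They refer to trained physicians without saying where they work, and to a multidisciplinary team without saying whether it is joint or one per site. Guidelines are given as a common basis for treatment. Nor does anything suggest that patients move between hospitals for their serial measurements.

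**Conclusion.** The point holds in a limited form. The stated stratification factors omit centre in a non-randomised two-hospital study whose group tests are unadjusted. Bias needs two things together: a hospital difference in resting pressure and an unequal treatment mix. Without either one it is zero. Under the assumed offsets and shares it runs from negligible (0.4 mmHg) to about a quarter of the planning difference (3.0 mmHg). The documents do not show that the hospitals differ in pressure readings, surgery or treatment mix. The case for change is that the stated plan would neither reveal nor remove such a difference, and that the remedy is cheap.

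**What to change.** Add centre to the factors named in the Discussion, and carry it into the Statistical methods section as a stratum or fixed effect in every between-group comparison of average resting pressure and the secondary outcomes. Where a rank test is used, use a centre-stratified version. Report the number of patients on each treatment at each hospital, so that readers can see how far treatment and centre overlap.

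Centre is already known and recruitment is planned to run to December 2026, so no new data and no design change are needed. As a fixed effect it costs one degree of freedom. If it were fully crossed with age, sex and stage it would double the number of strata, which is a reason to prefer the fixed effect. The loss of precision is small at 60/40, moderate at 80/20, and serious only if treatment is almost separated by hospital. In that case the wide interval would correctly show that the data cannot tell treatment from centre.

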## Trial status

The trial recruitment started on 1 January 2023, and it is estimated to be complete by the end of December 2026.

## Data Availability

The datasets generated or analyzed during the current study are not publicly available due to the laws on privacy protection but are available from the corresponding author on reasonable request.

## Abbreviations

TME: Total mesorectal excision
LARC: Locally advanced rectal cancer
NCRT: Neoadjuvant chemoradiotherapy
FI: Fecal incontinence
QOL: Quality of life
LARS: Low anterior resection syndrome
NCT: Neoadjuvant chemotherapy
ECOG: Eastern Cooperative Oncology Group
IBD: Inflammatory bowel disease
CTCAE: Common Terminology Criteria for Adverse Events
ARP: Average resting pressure
BMI: Body Mass Index
CT: Computerized Tomography
PET: Positron Emission Tomography
MRI: Magnetic Resonance Imaging
TNM: Tumor, Node and Metastasis
CRF: Case report forms
SD: Standard deviation
